## Methods

### Study design and participants

This will be a randomized control trial in a hospital of Nepal with two parallel groups (1:1 ratio), delayed cord clamping (≥180 s) and early cord clamping (≤60 s). The study will be conducted in Paropakar Maternity and Women’s Hospital, a public funded tertiary centre for obstetric and gynaecological services in Kathmandu, Nepal.

In the hospital there are two separated delivery departments, high risk-labour room (LR) and low risk-Maternal and Neonatal Service Center (MNSC). At admission, according to the hospital protocol, the pregnant women are screened by an obstetrician who made the decision to which department the women will be transferred.

The hospital criteria for admission to MNSC are-uncomplicated pregnancies, no complication at the time of admission and healthy mothers (no clinical history of hypertension, infection, diabetes, chronic medical condition), expected vaginal delivery, gestational age between 34 and 41 weeks and singleton pregnancy.

Women will be eligible to participate in the study if they are assigned to MNSC. The exclusion criteria will be serious congenital malformation, syndromes, or the other congenital disease that could affect the outcome measures. Written consent will be obtained from the women who were eligible and willing to participate (Fig. 1).

**Fig. 1 Fig1:**
[figure not shown]
Trial profile (CONSORT flowchart)

### Randomization

The principal investigator will prepare a random list using random digit generator in Microsoft excel and will not have clinical involvement in the trial. Following this, he will prepare sequentially numbered, opaque envelopes and put in the colour cards with details of the allocated group and sealed the envelopes.

These will be kept at the research office and will be brought in the delivery unit before randomization.

Randomization will take place a few minutes before delivery when the nurse-midwife considered vaginal delivery is imminent. To allocate the women into treatment group, the surveillance officer (SO) will open the next consecutively numbered envelope and inform the nurse-midwife of the assigned treatment. The used colour card and envelope will be discarded.

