### Surveillance protocol

Before the study period, early clamping was predominately practiced at the hospital. During the study period, surveillance officers (SO) are stationed 24 h a day at three stations, the reception, the delivery ward, and the postnatal wards. SO are all trained nurse-midwives.

As the pregnant woman arrives at the hospital, she will receive written information about the study in the reception. A SO will then approach the woman and ask for her consent to participate in the study.

If the woman agrees, she will sign the consent form and the SO stationed at the reception will register the information needed according to protocol. The woman’s labour will be managed by following the hospital’s ordinary routine until she is transferred to the delivery ward, where the randomisation takes place. The SO stationed at the delivery ward will pair the woman with a sealed, numbered, opaque envelope containing the treatment allocation and show this to the nurse-midwife conducting the delivery.

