### Intervention

When delivery is imminent (expected within 10 min), the nurse-midwife will open the sealed, numbered, opaque envelope to reveal the treatment allocation. The interventions consist of delayed clamping of the umbilical cord (≥180 s after delivery) or early clamping of the umbilical cord (≤60 s). The SO will measure the time from complete delivery of the baby until the first clamp is placed on the umbilical cord with a stopwatch. All other aspects of obstetric care will be managed according to standard practice at the hospital. Should the infant need resuscitation, the umbilical cord will be clamped and cut and the infant will be carried to the resuscitation table for further handling. In both groups, oxytocin will be given to the mother after the umbilical cord is clamped. All staff in the delivery unit will be trained in the study procedures before the trial is started.

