### Blinding

The study design precluded either the mother giving birth or the nurse-midwife performing the intervention being blinded. Physicians performing neonatal examinations, staff members responsible for collection of blood samples and background data, and laboratory staff performing analyses of blood samples will be blinded to each infant’s allocation group.

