### Data management

The SO will fill up and assess data records. The two research managers will verify all record forms with the primary source of data. A data entry officer will re-check them for discrepancies before entering the data in computers. The quality control team from Uppsala University will provide oversight to ensure quality of data collection and to avoid data loss. A protocol for data tracking will be followed. All cases will be analysed on an intention to treat basis.

The Census and Survey Processing System (CSPro), a public domain software package developed and supported by the U.S. Census Bureau and ICF Macro, will be used for quality data management. CSPro is interfaced with SPSS (originally, Statistical Package for the Social Sciences, 20), which will be used for statistical analysis, data management (case selection, file reshaping, creating derived data), and data documentation. Hard copies of records will be stored in a filing system in a secure room. Data will be checked for accuracy, consistency, and completeness in both CSPro and SPSS. An analysis plan will be developed in accordance with the reporting guidelines. A profile and comparison of key variables between groups at baseline will be presented.

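### The rule to discard used allocation cards and envelopes destroys the source record of the assigned arm, and two sections disagree on who opens the envelope

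*Protocol article*

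**What the plan says.** All of this is in the protocol article.

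- **Randomization, preparation.** "The principal investigator will prepare a random list using random digit generator in Microsoft excel and will not have clinical involvement in the trial". The same person makes up the envelopes: "he will prepare sequentially numbered, opaque envelopes and put in the colour cards with details of the allocated group and sealed the envelopes".
- **Randomization, opening.** Shortly before delivery, "the surveillance officer (SO) will open the next consecutively numbered envelope and inform the nurse-midwife of the assigned treatment". The section then closes with the rule "The used colour card and envelope will be discarded".
- **Surveillance protocol.** "The SO stationed at the delivery ward will pair the woman with a sealed, numbered, opaque envelope containing the treatment allocation", and shows it to the nurse-midwife conducting the delivery. It does not say who opens it.
- **Intervention.** "the nurse-midwife will open the sealed, numbered, opaque envelope to reveal the treatment allocation". The SO times the first clamp with a stopwatch.
- **Blinding.** "The study design precluded either the mother giving birth or the nurse-midwife performing the intervention being blinded". Neonatal examiners, staff collecting blood samples and laboratory staff are blinded.
- **Data management.** Two research managers check the record forms against the primary source, and "All cases will be analysed on an intention to treat basis".

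**The concern.** An intention-to-treat analysis needs the arm assigned to each woman, and that arm should be verifiable independently of what was done to her. With envelope randomization, the opened card and its numbered envelope are the physical evidence of which allocation was drawn, and they were prepared by someone outside the delivery unit. The article does not merely leave their fate unstated. It orders them thrown away.

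The conflict over the opener adds to this. Under one section the opener is research staff. Under the other it is the clinician who judges when delivery is imminent, which triggers randomization, who carries out the clamping and who cannot be blinded. The Surveillance protocol section says early clamping was the prevailing practice before the study, so departures towards habit are conceivable. At stake is whether an envelope opened early, taken out of turn, misread or altered could be recognised afterwards, and who would answer for it.

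**Working it through.** No figure in the article depends on this point, so the check compares sections and asks what evidence would be left.

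**Step 1: the opener.** Randomization: the SO opens and tells the nurse-midwife. Surveillance protocol: the SO pairs and shows, opener unnamed. Intervention: the nurse-midwife opens. The first and third cannot both be followed, and the second does not settle it.

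**Step 2: what the research managers could verify against.** For the assigned arm, the source at the point of allocation is the card. Once it is discarded, three things are left:

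- the arm written on the record form;
- the random list, which can be used for a given woman only if her envelope number or place in the randomization order was recorded;
- the stopwatch time, which shows treatment received. The Intervention section has the cord clamped and cut if the infant needs resuscitation, so a short time in an infant assigned to delayed clamping is compatible with correct allocation. The time cannot stand in for the card.

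**Step 3: what each kind of deviation would leave behind.**

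| Deviation | List plus recorded envelope number | With marked card and envelope also kept |
|---|---|---|
| Arm copied wrongly to the form | Shows as a mismatch with the list | Mismatch is seen and the true arm confirmed |
| Card misread or altered | Shows as a mismatch, cause unknown | Card shows what was drawn, or that it was changed |
| Envelope taken out of turn, its own number recorded | Arm agrees with the list; seen only if number order is compared with time of randomization or birth | ID and time on the envelope show the order |
| Envelope opened early, then used | Arm agrees with the list; nothing shows | Physical state and marked time give some evidence |

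If the envelope number was not recorded, the middle column largely falls away.

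**Step 4: scale of the remedy.** 270 newborns per group in two groups gives 2 × 270 = 540 cards and envelopes to keep.

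**The case against.** The strongest reply is that the allocation is better protected than the discard rule suggests. The list was made by someone without clinical involvement. Envelopes are sealed, opaque, consecutively numbered and opened only when delivery is near. Consent is taken earlier, at reception. Staff are trained, and blood collection and laboratory work are blinded. The article also condenses a fuller protocol, so an allocation log or an envelope-number field may well exist; their absence here is not a finding. All of this stands, and it limits the point to the two things that the article states outright: the discard rule and the conflicting opener.

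Two stronger readings are tempting and should be resisted.

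- **A reader might infer that a deviation would leave no trace.** That does not follow. The list and the envelope numbers survive, and the table above shows that some deviations would be detectable if the number was recorded.
- **A reader might infer a loss of power from mislabelled arms.** If a fraction e of infants in each arm carried the wrong label at random, the planned contrast would shrink from 0.15 to 0.15 × (1 − 2e). The documents give no value for e, and discarding a card does not cause mislabelling; it removes one means of finding it. The model also describes copying errors. An infant whose envelope was taken early or out of turn would usually be treated and recorded according to the card opened, so the threat there is selection, which the formula does not address.

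Calling the trial open also needs care. Mother and midwife are unblinded, but those who collect and analyse the blood are not. The exposure lies in allocation and delivery of treatment more than in measurement of haemoglobin. Blinded measurement does not, however, protect against selection at allocation.

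**Conclusion.** The point holds in a limited form. The article orders the destruction of the point-of-allocation source for the assigned arm, while its own data checks and intention-to-treat analysis depend on that arm being right. It also gives two incompatible answers on who opens the envelope. Out-of-order opening, or a misread or altered card, becomes much harder to detect, though not undetectable.

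The size of the risk is unknown and cannot be derived from the documents. How much checking remains possible rests on one unknown: whether each woman's envelope number or randomization order was recorded. Nothing here shows that allocation failed, and the sample size is unaffected. This is an inexpensive weakness to repair and should be repaired.

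**What to change.** - Replace the discard sentence in the Randomization section with a retention rule: the opener writes study ID, date and time on the sealed envelope and in a log before opening it, and every opened card and envelope is kept.
- Have someone outside the delivery unit reconcile the retained envelopes, the log and the recorded arms with the random list when enrolment ends.
- Make the Randomization, Surveillance protocol and Intervention sections name the same opener, preferably the SO and not the midwife who clamps the cord.

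The cost is changed wording, a log sheet and storage of 540 envelopes. No extra staff are needed, and no arm, endpoint or sample size changes. Retention makes subversion easier to detect but does not prevent it, since delivery-ward staff would still do the marking.

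The Timeline section plans enrolment over 45 to 60 days from October 2, 2014, before the article's publication in March 2016. If the cards have already been discarded, the trial report should state who opened the envelopes, whether envelope numbers were recorded, and the result of comparing recorded arms with the random list.

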### Surveillance protocol

Before the study period, early clamping was predominately practiced at the hospital. During the study period, surveillance officers (SO) are stationed 24 h a day at three stations, the reception, the delivery ward, and the postnatal wards. SO are all trained nurse-midwives.

As the pregnant woman arrives at the hospital, she will receive written information about the study in the reception. A SO will then approach the woman and ask for her consent to participate in the study.

If the woman agrees, she will sign the consent form and the SO stationed at the reception will register the information needed according to protocol. The woman’s labour will be managed by following the hospital’s ordinary routine until she is transferred to the delivery ward, where the randomisation takes place. The SO stationed at the delivery ward will pair the woman with a sealed, numbered, opaque envelope containing the treatment allocation and show this to the nurse-midwife conducting the delivery.

### Intervention

When delivery is imminent (expected within 10 min), the nurse-midwife will open the sealed, numbered, opaque envelope to reveal the treatment allocation. The interventions consist of delayed clamping of the umbilical cord (≥180 s after delivery) or early clamping of the umbilical cord (≤60 s). The SO will measure the time from complete delivery of the baby until the first clamp is placed on the umbilical cord with a stopwatch. All other aspects of obstetric care will be managed according to standard practice at the hospital. Should the infant need resuscitation, the umbilical cord will be clamped and cut and the infant will be carried to the resuscitation table for further handling. In both groups, oxytocin will be given to the mother after the umbilical cord is clamped. All staff in the delivery unit will be trained in the study procedures before the trial is started.

### Follow-up

After delivery, the babies will be cared for according to standard clinical routines, and early breast-feeding will be encouraged. As part of the study, the nurse-midwife will assess the infant at 1 and 6 h, to see whether the baby has been breastfed Infants will stay at the postnatal ward with their mothers for two or three days after delivery, except for those well babies whose mothers prefer to leave the hospital earlier and infants who require admission to the neonatal unit. The SO stationed at the postnatal ward will perform transcutaneous bilirubin measurements when child and mother are discharged from the hospital, as well as 24 and 48 h after delivery if possible. The following information will be collected from maternal healthcare records: background information of the mother’s age and parity, babies’ weight, gestational age and Apgar score.

Monthly, up to 12 months of age, a SO will call the family and ask questions regarding infections, breast-feeding and immunizations of the infant.

At 8 and 12 months of age, infants will be scheduled for a follow-up visit including blood sampling (haemoglobin and ferritin). Venous blood sampling will be performed. Mother’s will be interviewed about the infant’s feeding practice.

At 12 months of age, the Ages & Stages Questionnaire will be used to record infants’ neurodevelopment. Parents will be assisted in answering the Ages & Stages Questionnaire.

If funding is obtained, the Bayley Scales of Infant and Toddler Development, third edition will be used to examine children at 18–24 months of age.

### Blinding

The study design precluded either the mother giving birth or the nurse-midwife performing the intervention being blinded. Physicians performing neonatal examinations, staff members responsible for collection of blood samples and background data, and laboratory staff performing analyses of blood samples will be blinded to each infant’s allocation group.

### Sample size

The sample size for the primary outcome at eight months was estimated in order to find a difference of 15 % (70 versus 55 %) in the prevalence of anaemia between the two randomization groups with a power of 80 % and a type I error rate of .05. Using Fisher’s exact-test to analyse outcome data, a group size of 176 would be needed. Taking into account an attrition rate of 35 % we calculated that 270 newborns should be included in each group, i.e. a total of 540.

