## Background

At the time of birth, the infant is still attached to the placenta via the umbilical cord. The infant is usually separated from the placenta by clamping the cord with two clamps, and cutting between the clamps. This task takes place during the third stage of labour, which is the period of time from the birth of the infant to the delivery of the placenta [1].

Active management of the third stage of labour has been described in a recent World Health Organization (WHO) report as the “cornerstone” of obstetric and midwifery practice during the latter part of the 20th century [2]. Active management has involved the clinician intervening in the process of placental delivery through three interrelated practices: the administration of an uterotonic drug; early cord clamping and cutting; and controlled traction of the umbilical cord.

Early cord clamping has generally been advised to be completed within the first 30 s after birth, regardless of whether cord pulsation has ceased [3]. Due to evidence shown in the last decade, recent guidelines for active management of the third stage of labour no longer recommend immediate cord clamping [4], but changes in practice are still questioned [5] and policies in hospitals are rare [6].

Delayed clamping allows time for a transfer of the foetal blood in the placenta to the infant at the time of birth. This placental transfusion can provide the infant with an additional 40 % more blood volume [7]. The amount of blood transferred to the infant depends on when the cord is clamped and at what level the infant is held prior to clamping [8]. Neonatal benefits associated with this increased placental transfusion include higher haemoglobin concentrations, additional iron stores and less anaemia in early infancy and better cardiopulmonary adaptation [1, 9, 10].

Delayed cord clamping has, however, been linked to an increase in the incidence of jaundice which, in severe cases, could have longer-term effects on the health and development of the infant [1, 11].

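### Fisher's exact test, the only test the article names, is valid but conservative at 176 per arm; a risk difference adjusted for gestational age would be a free gain in efficiency

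*Protocol article*

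**What the plan says.** All references are to the protocol article.

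- **Sample size.** The trial is sized to "find a difference of 15 % (70 versus 55" %) in anaemia prevalence at eight months, "with a power of 80 % and a type I error rate of .05". The method is Fisher's "exact-test to analyse outcome data, a group size of 176 would be needed". The enrolment target follows: "Taking into account an attrition rate of 35 % we calculated that 270 newborns should be included in each group".
- **Primary outcome.** Haemoglobin at 8 months is named as primary, with anaemia defined by a cut-off of 110 g/L after altitude correction.
- **Study design and participants; Randomization.** Gestational ages of 34 to 41 weeks are admitted. Allocation follows a random list, and no stratification is described. The envelope is opened shortly before delivery.
- **Follow-up.** The background data taken from maternal records are maternal age and parity, and the baby's "weight, gestational age and Apgar score".
- **Data management.** Analysis is by intention to treat and an analysis plan is to be developed. "A profile and comparison of key variables between groups at baseline will be presented"; the variables are not listed.

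**The concern.** Fisher's test appears as the method for the outcome data and not only as a device for obtaining a sample size, so it is a stated choice. With about 176 infants per arm and prevalences of 55-70%, there is no small-sample reason for an exact conditional test. Such a test rejects less often than its nominal level allows, and it cannot use a covariate or give an adjusted effect.

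Gestational age is a natural candidate covariate here. The sample mixes late pre-term and term infants, no stratification is described, and the variable is settled before the cord is clamped and already collected. A method that cannot use it forgoes whatever precision it offers.

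A smaller, related point concerns the variables listed with it. Birth weight and Apgar score are recorded after randomisation and after clamping. The Background says of delayed clamping: "This placental transfusion can provide the infant with an additional" 40% of blood volume. Both variables could therefore be affected by treatment. If they entered a baseline comparison or an adjusted model, a treatment effect could be misread as imbalance, or part of it could be adjusted away.

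**Working it through.** **Inputs (Sample size section).** p1 = 0.70, p2 = 0.55, difference d = 0.15, power 80%, type I error 0.05, 176 evaluable per arm, attrition 35%. Sidedness is not stated. Two-sided is assumed because it reproduces the article's figure; one-sided gives 128, or 141 with continuity correction.

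**Step 1: reproduce 176.** With p̄ = 0.625, the uncorrected formula is

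n = [1.960·√(2·0.625·0.375) + 0.842·√(0.70·0.30 + 0.55·0.45)]² / 0.15²

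= [1.960·0.6847 + 0.842·0.6764]² / 0.0225 ≈ 162.3, so 163 per arm.

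The continuity correction, which approximates Fisher's test, is

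n' = (n/4)·[1 + √(1 + 4/(n·d))]² = (162.3/4)·[1 + √(1 + 4/24.35)]² ≈ 175.4, so 176 per arm.

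This matches the article. For attrition, 176/0.65 = 270.8, so 271 against the stated 270, which is immaterial.

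**Step 2: exact behaviour at 176 per arm.** All pairs of binomial counts were enumerated. Power is the probability of rejection at 0.70 against 0.55. Size is the probability of rejection when both arms share one rate.

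| Test (two-sided) | Power | Size at 0.55 | Size at 0.625 | Size at 0.70 |
|---|---|---|---|---|
| Fisher | 0.8057 | 0.0368 | 0.0396 | 0.0382 |
| Mid-p Fisher | 0.8320 | 0.0475 | 0.0502 | 0.0483 |
| Pearson chi-square | 0.8355 | 0.0477 | 0.0518 | 0.0497 |

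Over a grid of common rates from 0.01 to 0.99, the largest size of Fisher's test is 0.0396.

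**Step 3: the cost.**

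- In power: 0.8355 − 0.8057 = 0.030 against chi-square, and 0.8320 − 0.8057 = 0.026 against mid-p.
- In infants: chi-square has exact power 0.8006 at 163 per arm. The difference is 176 − 163 = 13 evaluable infants per arm, and 13/176 = 7.4%.
- In enrolment at 35% attrition: 163/0.65 = 250.8, so 251 against 271. That is 20 per arm, or 40 in all.

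**Step 4: gestational age.** The gain from adjustment depends on how strongly gestational age predicts anaemia or haemoglobin in this sample. The article gives neither that association nor the share of late pre-term infants, so no figure can be derived.

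**The case against.** The strongest reply is that nothing here is wrong. The 5% is a ceiling, and Fisher's test respects it. The 176 was calculated for that test and delivers 80.6%, so the design has already paid for the conservatism. The suggested chi-square slightly exceeds 5% at some rates (5.18% at 0.625). All of this stands, and it rules out a claim of error. It does not remove the avoidable loss of about 3 points of power.

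A reader might infer more in four places, and the article does not support it:

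- **That the type I error is misstated, or that power falls short.** Neither is so, as Step 2 shows.
- **That gestational age will be ignored.** Fisher's test is named only in the sample-size paragraph, and a separate analysis plan is announced that may well specify covariates. Randomisation also makes the unadjusted comparison valid, and chance imbalance is already allowed for in the error rate. Adjustment would add precision only.
- **That adjustment is worth a known number of infants.** If gestational age explained 2-10% of the variance, 176/(1 − R²) − 176 would give about 4 to 20 per arm. That R² is assumed, and it concerns haemoglobin, whereas 176 was derived for anaemia. The figure should not be used.
- **That birth weight will be adjusted for, or is distorted by a known amount.** The article proposes no such adjustment. Taking 40% of an assumed 70-80 mL/kg at 3 kg gives 84-96 mL, or roughly 90-100 g. This is at most an upper bound: the early arm may be clamped as late as 60 s, and no between-arm difference in transfusion is given.

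The article also names haemoglobin as primary while sizing on anaemia. That is a separate matter, and this point does not rest on it.

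**Conclusion.** This is a free improvement and not a validity error. Fisher's test is a legitimate choice that meets the stated power. At the planned size it runs at about 3.7-4.0% instead of close to 5%, and it costs 2.6 to 3.0 points of power against mid-p or chi-square, or 13 evaluable infants per arm.

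These figures assume a two-sided test, exactly 176 evaluable infants per arm, and the article's own prevalences. They describe the unadjusted comparison. Any further gain from gestational age is plausible but cannot be sized from the article. The remark on birth weight and Apgar score is a precaution, since the article does not say how they will be used.

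**What to change.** In the analysis plan that the article announces, and before outcomes are examined by arm:

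1. Analyse anaemia at 8 months by a risk difference adjusted for gestational age, from logistic regression with standardisation, with its 95% confidence interval. Name Pearson's chi-square or mid-p Fisher as the unadjusted test. Choose mid-p if staying nearer to the 5% ceiling matters more.
2. Analyse haemoglobin at 8 months by linear regression on arm and gestational age.
3. If baseline variables or covariates are listed, label birth weight and Apgar score as post-randomisation. Report them by arm, but do not use them for adjustment or as evidence of baseline balance. Maternal age and parity are fixed before randomisation and raise no such problem.

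The cost is wording only. Every variable needed is already being collected, and the enrolment target of 270 per arm can stay as it is.
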